#### 2.5.4. Sample Size Calculation

After interventional treatment for patients with coronary heart disease (CHD), according to the reference literature, the difference in the amplitude of the increase in peak oxygen consumption was 3.33 mL/(min(/), the standard deviation was 3.65 mL/(min(/), the error of class I was 0.05, and the test efficiency was 90%. The following formula was used to calculate the sample size of each group:(1)$$\begin{array}{c} n=\frac{2{\left(\mu_{\alpha }+\mu_{\beta }\right)}^{2}\sigma^{2}}{\delta^{2}}. \end{array}$$

The sample size of each group was 26; considering a 20% rate of shedding, 33 samples were calculated. According to the order of entering the group, 33 cases will be randomly divided into the QSYQ group and the blank placebo control group.

### 2.6. Interventions

#### 2.6.1. Drug Elution

The trial will involve drug elution for 1 week in the screening period before enrollment, that is, stopping other TCM used for CHD, including decoctions, Chinese patent medicine, and substitute tea.

#### 2.6.2. QSYQ Group

Standardized drugs combined with QSYQ will be administered for 12 weeks. The standardized drugs will include dual-antiplatelet, lipid-lowering, antihypertensive, hypoglycemic, and other symptomatic treatments; QSYQ is administered 1 bag at a time (0.5 g/bag), 3 times a day, taken 30 min after a meal.

#### 2.6.3. Blank Placebo Control Group

The patients will be treated with standardized Western medicine combined with placebo for 12 weeks. The standardized drugs will include dual antiplatelet, lipid-lowering, antihypertensive, hypoglycemic, and other symptomatic treatments; placebo is administered 1 bag at a time (0.5 g/bag), 3 times a day, taken 30 min after a meal.

### 2.7. Follow-Up

Following enrollment, all subjects will be followed up every 2 weeks, and the researchers set the content of each follow-up. After 8 weeks, all subjects will be followed up every 4 weeks until the end of the 12-week study. Follow-up will involve recording changes in TCM symptoms, Seattle scale score, and quality of life scale score.

## 3. Outcome

The primary outcome is the rate of change of VO_2_ peak. The secondary outcomes are as follows: (1) assessment of target organ damage, including changes in systolic and diastolic function indices (left ventricular ejection fraction, stroke output, left ventricular end-diastolic volume, *E*/*E*′, left atrial volume, etc.) in echocardiography observed before and after treatment; (2) symptom improvement evaluation using the TCM syndrome observation table (Table 2); Seattle scale and quality of life scale will be used to evaluate angina pectoris symptoms and quality of life; and (3) routine laboratory examination indicators, including routine bloods, liver and kidney function, and blood lipids.

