### 3.3. Data Analyses

The international SAS version 9.4 statistical analysis software will be used for statistical analysis. The measurement data of each visit for different treatment groups will be statistically described by means of mean *u* standard deviation or median (minimum and maximum). Paired *t*-test will be used to compare the differences between the two groups. Changes before and after treatment in the two groups will be compared by analysis of variance or nonparametric test. The frequency (constituent ratio) will be used to describe the count data of each visit in different treatment groups. The changes before and after treatment in the two groups will be analyzed using the *χ*2 test, exact probability method, or nonparametric test. Except for special instructions, the bilateral test will be used to examine statistical significance, and *P* ≤ 0.05 will be used as the criterion for judging the significance of the difference.

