**Figure 2 fig2:**
[figure not shown]
Research technology roadmap.

**Table 1 tab1:** Diagnostic criteria of Qi deficiency and blood stasis syndrome.

	Signs and symptoms
Symptoms	A: fatigue, shortness of breath, and physical weakness, with aggravation after activity; B: purple and dark lip color
Tongue presentation	The tongue is dark or has ecchymosis and ecchymosis; the sublingual vein is tortuous, dilated, and dark purple
Pulse condition	Weak pulse, astringent pulse
Diagnosis	One of A and one of B; or one of A and one abnormal tongue presentation pulse image for clinical diagnosis reference

**Table 2 tab2:** TCM syndromes observation table.

Definition	Meaning
Clear effect	Clinical symptoms and signs were significantly improved, and the syndrome score was reduced by 70%
Valid	Clinical symptoms and signs were improved, and the syndrome score decreased by 30%
Invalid	Clinical symptoms and signs were not significantly improved, or even aggravated, and the syndrome score was reduced by <30%
Aggravation of symptoms	Clinical symptoms and signs were aggravated, and the syndrome score decreased by < 0

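### The TCM symptom outcome is a four-class cut of a numeric score, and the listed tests include ones that ignore class order; the plan never commits to comparing the score itself

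*Protocol article*

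**What the plan says.** Section 3 (Outcome) puts symptom evaluation by Table 2 among the secondary outcomes: "symptom improvement evaluation using the TCM syndrome observation table (Table 2". Table 2 has four rows, each pairing a clinical description with a change in the syndrome score:

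- Clear effect, cut at 70%: "Clinical symptoms and signs were significantly improved, and the syndrome score was reduced by 70"
- Valid, cut at 30%: "Clinical symptoms and signs were improved, and the syndrome score decreased by 30"
- Invalid, below 30%: "and the syndrome score was reduced by <30"
- Aggravation, below 0: "Clinical symptoms and signs were aggravated, and the syndrome score decreased by < 0"

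A percentage reduction needs a numeric score before and after treatment, so the score must be collected. Section 2.7 also has changes in TCM symptoms recorded at follow-up.

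Section 3.3 (Data Analyses) has two relevant sentences. For count data: "The changes before and after treatment in the two groups will be analyzed using the *χ*2 test, exact probability method, or nonparametric test". For measurement data: "Changes before and after treatment in the two groups will be compared by analysis of variance or nonparametric test". Neither is tied to the TCM outcome. Tests are two-sided at 0.05.

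**The concern.** The form in which this outcome is defined, a class, holds less information than the score it is built from. Reductions of 31% and 69% fall in the same class, while 29% and 31% fall in different ones. Two of the three tests listed for count data, chi-square and exact, also take no account of the order of the classes: shuffling the four labels would leave the p-value unchanged.

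The trial enrols patients by TCM syndrome, and this is the only TCM-specific efficacy outcome in Section 3. With about 26 evaluable patients per arm, a real symptom benefit could be reported as not significant because of the test chosen, although the data for a better test are already in hand. The article gives no reason or outside requirement for testing the classes rather than the score.

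**Working it through.** **1. The plan's own figure.** Section 2.5.4 gives a difference of 3.33, SD 3.65, alpha 0.05 and power 90% for peak oxygen consumption. n = 2 × (1.960 + 1.282)² × 3.65² / 3.33² = 25.25, rounded up to 26 per arm. With 20% dropout, 26 / 0.8 = 32.5, rounded up to 33. Both figures reproduce. Nothing comparable is given for the syndrome score.

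**2. Inputs for the comparison.**

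- From the document: 26 evaluable per arm, 1:1 allocation, two-sided 0.05, cuts at 0, 30% and 70%.
- Assumed: percentage reduction normal, SD 30 points, placebo mean 20 or 35.
- Assumed standardised effect: 0.5, 0.7 or 0.91, that is 15, 21 or 27.4 points. The last is 3.33 / 3.65 = 0.912, borrowed from peak oxygen consumption for want of anything better.
- Classes read as below 0, 0 to under 30, 30 to under 70, and 70 or more, set by the score alone.

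**3. Class probabilities, one example.** P(class) is the normal probability between cuts. With placebo mean 20, P(below 0) = Φ((0 − 20)/30) = Φ(−0.667) = 25.2%, and the four classes from worst to best are 25.2, 37.8, 32.2 and 4.8%. With the active mean at 47.4 they are 5.7, 22.4, 49.3 and 22.5%.

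**4. Power by simulation** (20,000 trials per row; simulation error about 0.4 points at most). The tests are a two-sample t-test on the percentage reduction, Pearson chi-square on the 2×4 table, and a Wilcoxon rank-sum test on the four ordered classes.

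| Effect | Placebo mean | t-test on score, % | Chi-square, % | Rank test on classes, % | Chi-square loss | Rank-test loss |
|---|---|---|---|---|---|---|
| 0.5 | 20 | 42.0 | 22.7 | 36.5 | 19.3 | 5.5 |
| 0.5 | 35 | 43.1 | 22.5 | 36.8 | 20.6 | 6.3 |
| 0.7 | 20 | 69.4 | 43.8 | 62.3 | 25.6 | 7.1 |
| 0.7 | 35 | 69.9 | 42.8 | 61.9 | 27.1 | 8.0 |
| 0.91 | 20 | 89.6 | 68.6 | 84.1 | 21.0 | 5.5 |
| 0.91 | 35 | 89.6 | 66.4 | 83.8 | 23.2 | 5.8 |

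**5. Where the loss comes from.** In the effect 0.91, mean 20 row, the chi-square loss of 21.0 points splits into 84.1 − 68.6 = 15.5 from ignoring order and 89.6 − 84.1 = 5.5 from cutting. Ignoring order is 15.5 / 21.0 = 74% of the loss. In the 0.5, mean 35 row it is (36.8 − 22.5) / 20.6 = 69%.

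**6. Sensitivity.** With control means 15 to 40, SDs 20 to 40 and 26 or 33 per arm, the chi-square loss runs from about 15 to 30 points and the rank-test loss from about 3 to 10.

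An exact test on the full 2×4 table was not simulated. It shares the indifference to order, but no figure is claimed for it. Nor is the further effect of adjusting for the baseline score quantified.

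**The case against.** The best defence is that Section 3.3 already permits a good test. The count-data sentence ends with a nonparametric test, the list is not ranked, and a rank test on the ordered classes keeps most of the power. That stands. A reader might infer that the classes will be tested by chi-square and that about 20 points of power will be lost; the article assigns no test to this outcome, so the loss belongs to one permitted option. Nor may it be blamed on the cutting, which by itself costs only 5 to 8 points in the main scenarios.

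The score might also be analysed under the measurement-data sentence. The article neither excludes nor commits to this, while defining the outcome by the Table 2 classes.

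Two further readings should be resisted. Pooling the classes into responders and non-responders at 30% would lose more, but no section proposes it. And each row of Table 2 adds a clinical judgement to the score, so the class is not a pure function of the score, as the simulation assumes.

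Finally, one may say that choosing among listed tests for a secondary outcome belongs in an analysis plan. That would answer a complaint about missing detail. The point here is different: the article fixes a class-based outcome and lists tests that waste its order, when a better analysis of data already collected is available. It remains a minor point.

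**Conclusion.** The point holds as a cheap improvement, not as an error in the trial's main inference. The outcome is defined by a four-class cut, tests blind to class order are allowed on it, and no section commits to comparing the score. Under the stated assumptions, choosing chi-square would cost about 19 to 27 points of power against analysing the percentage reduction (15 to 30 on the wider grid). Choosing a rank test on the classes would cost about 5 to 8 (3 to 10 on the wider grid).

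These sizes rest on a normal distribution, spreads and effects that the article does not supply for this score. A reader might infer that the trial is underpowered; the documents do not support that, because this is a secondary outcome with no stated power, and the primary outcome and the 33 per arm are untouched.

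**What to change.** In Sections 3 and 3.3, make the tested TCM outcome the week-12 syndrome score, or its change from baseline, compared between arms by ANCOVA with the baseline score as covariate, or by a rank test if the score is skewed. Report the Table 2 classes by arm as a descriptive table. If a test on the classes is wanted, name an ordered one (Wilcoxon rank-sum or proportional odds) in place of chi-square or an exact test.

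The cost is wording only, since the score is needed anyway to assign the classes. The one drawback is presentational: the headline TCM result becomes a difference in score rather than the customary response rate, which would still be tabulated.

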### 3.1. Safety Assessment and Adverse Events Report

To evaluate the safety of Qishen Yiqi dripping pills and placebo, we will investigate abnormal changes in laboratory examination results before and after treatment and other adverse events. Once adverse events (including major adverse events) occur during the treatment, the occurrence time, clinical manifestations, treatment process and duration of adverse events, outcome, and the relationship with drugs will be recorded in detail on the case report form. Patients with laboratory abnormalities will be followed until the test results return to normal, to the preadministration level, or until it is determined that the adverse event is unrelated to the test drug. If a serious adverse event occurs, the Serious Adverse Event Form will be completed and reported to the Ethics Committee within 24 h.

### 3.2. Data Management

In this study, case report form (CRF) tables will be used to collect data. The subject information will not be directly recorded in the CRF but will be recorded on the original medical record of each subject, which will be retained as the original data. Medical and other records of subjects will be maintained by the investigator. These records should include the following: original data, copies of laboratory data, and results of other medical tests (e.g., electrocardiogram, etc.). The data in the CRF table will be taken from the original medical records and filled in by the researcher or the person designated by the researcher. The completeness and accuracy of the information will be ensured. The name of the person who made the change and the date of the change will be immediately recorded for any changes made to the CRF table. Upon completion of the CRF, it shall be submitted to the Data Statistics Center of the China-Japan Friendship Hospital in time for confirmation following raw data verification (SDV), data manager (DM) review, questioning, and other processing. Before data locking, the researcher will confirm the completeness and accuracy of data by signature. This trial has been registered in the “China Clinical Trial Registry” (http://www.chictr.org.cn/index.aspx) before the formal start of the trial. To facilitate follow-up tracing and verify the authenticity of the data, the study data related to the trial will be uploaded to the above website and made public at the end of the trial. The registration number is ChiCTR2000040838 (registration date is December 11, 2020).

### 3.3. Data Analyses

The international SAS version 9.4 statistical analysis software will be used for statistical analysis. The measurement data of each visit for different treatment groups will be statistically described by means of mean *u* standard deviation or median (minimum and maximum). Paired *t*-test will be used to compare the differences between the two groups. Changes before and after treatment in the two groups will be compared by analysis of variance or nonparametric test. The frequency (constituent ratio) will be used to describe the count data of each visit in different treatment groups. The changes before and after treatment in the two groups will be analyzed using the *χ*2 test, exact probability method, or nonparametric test. Except for special instructions, the bilateral test will be used to examine statistical significance, and *P* ≤ 0.05 will be used as the criterion for judging the significance of the difference.

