### 2.5. Randomization, Allocation Concealment Mechanism, and Blinding

#### 2.5.1. Random Allocation

Randomization of subjects: studies have shown that the number of diseased vessels and complicated lesions (hypertension, diabetes, and other chronic diseases) are independent risk factors affecting the recurrence of cardiovascular events after PCI and significantly influence prognosis [18]. To reduce selection bias and balance various non-study factors between groups, two factors affecting the prognosis of interventional surgery were set in this study [19–21]: (1) sex, male or female and (2) number of diseased vessels, single-, double-, or multiple-branch lesions. An online dynamic random method will be used to design and allocate hiding. Subjects will be randomly divided into the QSYQ group and the placebo group at a 1 : 1 ratio. We plan to use the clinical trial data management platform commissioned by the China-Japan Friendship Hospital to generate the random number and group number with the “YinRuiDa Randomization and Drug Management System.” Following provision of informed consent, the patient's name and ID number will be input into the “YinRuiDa Randomization and Drug Management System,” and a random number and group number will be generated. The patient number for each subject will remain the same throughout the study.

Drug random grouping: each patient will receive the drug or placebo 3 times, every 28 days (*n* = 99 copies per group; 1 copy = 1 dose for 28 days per person). SAS version 9.4 statistical software will be used to generate numbers 1–198, with each dose for 28 days per person being allocated one number.

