The main hypotheses of this study are as follows: (1) most patients with CHD after interventional surgery suffer from Qi deficiency and blood stasis, and the long-term application of compound TCM to replenish Qi and activate blood circulation improves exercise endurance, reduces the risk of angina pectoris, reduces the rate of readmission, and improves quality of life; and (2) the effect of integrated traditional Chinese and Western medicine on CR is better than that of traditional exercise rehabilitation. The innovation points are mainly reflected in the following three aspects:A standardized measurement is needed to effectively assess changes in exercise endurance before and after treatment. We chose the rate of change of peak oxygen consumption (PeakVO_2_), the gold standard of exercise endurance, as the main result. Considering the indications and contraindications of cardiopulmonary exercise, patients with stable angina pectoris after coronary heart disease intervention were selected as the research object to avoid the occurrence of cardiovascular events, such as acute myocardial infarction, unstable angina pectoris, and malignant arrhythmias, caused by exercise.This program can give full play to the advantages of syndrome differentiation and treatment, early intervention, and multitarget of TCM and supplement the deficiency of simple rehabilitation methods of Western medicine. After syndrome differentiation, we will include patients with stable angina pectoris of Qi deficiency and blood stasis type. On the basis of conventional Western medicine treatment, QSYQ and placebo will be given orally.The study protocol was designed according to international clinical trial principles. A blank placebo randomized double-blind control was designed to ensure the authenticity and reliability of the research data. To reduce the selection bias caused by the number of enrolled cases, we used stratified randomization. Two stratification factors, “sex” and “number of disaffected vessels,” were set for randomization, with the purpose of reducing type I errors, improving the assurance of small sample trials and ensuring the balance of sample distribution between groups.

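### A paired t-test is named for comparing two independent, unmatched arms, and with the next sentence it leaves the test for the primary outcome unclear

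*Protocol article*

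**What the plan says.** Two consecutive sentences of section 3.3 (Data Analyses) deal with continuous measurements. The first reads "Paired *t*-test will be used to compare the differences between the two groups". The second reads "Changes before and after treatment in the two groups will be compared by analysis of variance or nonparametric test". Neither mentions the primary outcome.

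Other sections of the protocol article bear on this:

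- **Design, section 2.5.1:** "Subjects will be randomly divided into the QSYQ group and the placebo group at a 1 : 1 ratio". Allocation is by an online dynamic method.
- **Balancing factors, section 4:** "Two stratification factors, “sex” and “number of disaffected vessels,” were set for randomization". These balance the arms as groups. No section links an individual QSYQ patient to an individual placebo patient.
- **Primary outcome, section 3:** "The primary outcome is the rate of change of VO_2_ peak". It is itself a before/after change.
- **Sample size, section 2.5.4:** "The sample size of each group was 26", rising to 33 after 20% loss, from a formula with a leading factor of 2.

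**The concern.** A paired t-test analyses within-pair differences. It suits two measurements on one patient, or patients matched one to one by design. Neither applies to a comparison of QSYQ with placebo here. Three things follow if the first sentence is taken at its word:

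1. The analyst must invent pairs, for example by enrolment order or list position. Different inventions give different p-values from the same data.
2. The test needs equal numbers in the two arms. Section 2.4.4 lists reasons for removing patients and section 2.5.4 allows for 20% loss, so equal analysed numbers are not assured.
3. The stated test is not the one behind the sample size.

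The two sentences also overlap. The primary outcome is a change that will be compared between two groups, and both sentences can be read to cover it. One names a test that does not fit. The other offers two alternatives. In a 66-patient trial the reader should know beforehand which single comparison gives the primary result.

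**Working it through.** **Inputs.** From section 2.5.4: "the difference in the amplitude of the increase in peak oxygen consumption was 3.33" and "the standard deviation was 3.65", type I error 0.05, power 90%, 20% loss. From section 3.3: two-sided testing. Assumed for illustration only: observed differences of 1.8 and 2.0, and normally distributed data.

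**Step 1: reproduce the plan's own figure.** The formula is n = 2(z₁ + z₂)²σ²/δ², with z₁ = 1.960 (two-sided 0.05) and z₂ = 1.282 (90% power).

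- (1.960 + 1.282)² ≈ 10.507
- n = 2 × 10.507 × 3.65² / 3.33² = 2 × 10.507 × 13.3225 / 11.0889 = 25.25, rounded up to 26
- 26 / (1 − 0.20) = 32.5, rounded up to 33

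Both figures reproduce. A one-sided version would give 21, so the plan used the two-sided formula for two independent samples.

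**Step 2: power of each test at the design effect.** The standard error of the difference is σ√(2/n). Arbitrary pairing leaves it the same on average, but the degrees of freedom fall from 2n − 2 to n − 1.

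| n per arm | Noncentrality | Independent t: df, critical t, power | Paired on arbitrary pairs: df, critical t, power |
|---|---|---|---|
| 26 | 3.33/(3.65√(2/26)) = 3.29 | 50, 2.009, 89.7% | 25, 2.060, 88.5% |
| 33 | 3.33/(3.65√(2/33)) = 3.71 | 64, 1.998, 95.4% | 32, 2.037, 94.9% |

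The loss is 1.2 points at 26 per arm and 0.6 at 33.

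**Step 3: dependence on the pairing.** Suppose both arms have SD s and a given pairing happens to produce correlation r between the paired values. The paired standard error is then s√(2(1 − r)/n). The mean difference is fixed, but r changes with every reordering of the list.

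Take 26 per arm, s = 3.65 and an observed difference of 2.0:

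- Independent test: 2.0 / (3.65√(2/26)) = 2.0 / 1.012 = 1.976, p = 0.054.
- The paired test reaches p ≤ 0.05 when 1.976/√(1 − r) ≥ 2.060, that is r ≥ 1 − (1.976/2.060)² ≈ 0.08.
- Under random pairing r has mean 0 and SD 1/√25 = 0.20, so this should happen in about 34% of pairings.

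Simulation with 10,000 random pairings of one data set agrees:

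| Observed difference | Independent p | Paired p, central 95% | Pairings with p ≤ 0.05 |
|---|---|---|---|
| 1.8 | 0.081 | 0.033 to 0.145 | 10% |
| 2.0 | 0.054 | 0.018 to 0.105 | 34% |
| 3.33 | 0.002 | 0.0003 to 0.010 | 100% |

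The full range at 2.0 is 0.002 to 0.147. The pairing decides the verdict only when the result is near the threshold. At the design difference every pairing is significant.

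**Step 4: type I error.** In 100,000 simulated trials with no true difference, and one pairing fixed without regard to outcome, the paired test rejects in 4.97% and the independent test in 5.02%. Alpha is not inflated. It would be at risk only if the pairing were chosen after looking at the data, which an undefined pairing does not prevent.

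**Step 5: the two sentences side by side.** With two groups, analysis of variance on change is the same test as the independent two-sample t-test (F = t²) and agrees with the formula in section 2.5.4. The second sentence therefore can supply a proper primary test. Nothing says that it does, and the first sentence claims a between-group comparison for a different test.

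**The case against.** The strongest defence is that the first sentence is a slip of wording or translation. A common pattern is a paired t-test for before/after change within each arm, followed by analysis of variance or a nonparametric test for changes between arms. The two sentences fit that pattern well, and on its natural reading the second one covers the primary outcome. This largely stands: it is the likeliest intention, though the text cannot confirm it. It does not make the first sentence correct, because that sentence expressly compares the two groups.

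Three stronger readings are tempting, and the document does not support them.

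- **That the primary p-value will depend on arbitrary pairing.** No sentence ties the paired test to the primary outcome, and the analysis-of-variance sentence is also there to cover it. The paired sentence is not the only one naming a comparison involving both groups.
- **That efficacy will be judged by setting one within-arm p-value against the other, with many false positives.** No such decision rule is stated. If the first sentence does mean within-arm testing, the second supplies the between-arm comparison. Any error rate for such a rule would also need a size for the improvement common to both arms, which the document does not give.
- **That the trial is underpowered.** The sample size reproduces and suits an independent-groups test. Even the literal paired test costs only about 1 point of power.

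It may also be said that a journal article leaves model detail to a fuller plan. That would excuse silence, but this is a test stated wrongly.

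**Conclusion.** Wrong as written. A paired t-test is not a valid description of a comparison between two independent, unmatched arms, and it disagrees with the plan's own design and sample-size formula. Read with the sentence after it, it leaves open which test gives the primary result for the change in peak VO2.

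The size is limited. Taken literally, the cost is undefined pairs, a test that fails when the analysed arms are unequal, a p-value that moves with list order in borderline results, and a power loss of about 1 point at 26 per arm. Type I error stays at about 5% when the pairing is fixed independently of outcome. These figures assume normal data and the SD of section 2.5.4. The spread of p-values also rests on the assumed observed differences.

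**What to change.** Replace the first sentence and settle the primary test, for example:

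*Paired t-tests will be used only to describe before/after change within each group; no conclusion on efficacy will be drawn from them. The primary analysis is the between-group difference in change in peak VO2 from baseline to 12 weeks, tested two-sided by [one named independent-groups method] and reported as a mean difference with its 95% confidence interval.*

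Either a two-sample t-test (equivalently analysis of variance on change) or analysis of covariance with baseline peak VO2 would fill the bracket. Which one is a separate choice; correcting this point needs only that one be named. If a nonparametric alternative is kept, give the rule for using it in advance.

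The cost is a sentence or two of text. The sample size stays at 26 per group, 33 after dropout, and no patient or trial procedure is affected. Section 3.5 reports that recruitment is under way, so the change should be made and dated before database lock and before the first unblinding step in section 2.5.3.

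### The stated comparison of changes uses neither baseline peak VO2 as a covariate nor the two allocation factors, so it stays valid but gives up precision in a small trial

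*Protocol article*

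**What the plan says.** Section 3.3 (Data Analyses) gives the between-group analysis of continuous outcomes: "Changes before and after treatment in the two groups will be compared by analysis of variance or nonparametric test". Tests are two-sided ("the bilateral test will be used to examine statistical significance"). No covariate or factor is named. The same paragraph also names a paired t-test for comparing the two groups; that is a separate matter and is not pursued here.

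Section 2.5.1 (Random Allocation) uses an online dynamic method at 1:1 with two balancing factors: "1) sex, male or female and (2) number of diseased vessels, single-, double-, or multiple-branch lesions". The Discussion (section 4) calls this stratified randomisation and says the factors were set "with the purpose of reducing type I errors, improving the assurance of small sample trials", as well as for balance between groups.

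Section 3 (Outcome) makes the primary outcome the rate of change of peak VO2. Section 2.5.4 sizes the trial with the plain two-sample formula for means, without allowance for covariates.

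**The concern.** The design and the stated analysis do not match. Allocation is constrained so that sex and vessel number are alike in the two arms, but the comparison is then described as if allocation had been simple. If these factors predict the outcome, the balance removes part of the real variability of the treatment difference, while an unadjusted standard error still counts it. The reported interval is then too wide and the test rejects less often than its nominal level. The Discussion presents a reduction in type I error as a purpose of stratifying. A rate pushed below 5% in this way is lost sensitivity, not a benefit.

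Baseline peak VO2 is a second, separate source of precision. A change score generally stays correlated with the baseline value, and a covariate recovers that information.

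With about 26 evaluable patients per arm, precision is scarce, and the data needed to gain it are already in hand.

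**Working it through.** **Inputs from the article.** Difference: "the difference in the amplitude of the increase in peak oxygen consumption was 3.33". SD: "the standard deviation was 3.65". Error rates: "the error of class I was 0.05, and the test efficiency was 90" (per cent). Two-sided test, 1:1 allocation, 20% dropout.

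**Inputs not in the article (assumed, shown as ranges).** Correlation r between baseline and follow-up peak VO2: 0.5 to 0.9. Share of variance of the change explained by sex and vessel number together (R²): 0 to 0.30.

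**1. The plan's own figure.** n = 2(1.960 + 1.282)² × 3.65² / 3.33² = 25.25, rounded up to 26 per group. With dropout, 26 / 0.8 = 32.5, rounded up to 33. Both stated figures reproduce. Power of the unadjusted test with 26 per group is 90.8% by the normal formula and 89.7% by the non-central t.

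**2. Baseline as a covariate.** With equal variances at both times, Var(ANCOVA) / Var(change score) = (1 − r²) / [2(1 − r)] = (1 + r)/2. The working SD is 3.65 × √[(1 + r)/2].

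| r | variance ratio | SD | power at 3.33, n = 26, by t | n per group for 90% (normal formula) |
|---|---|---|---|---|
| no adjustment | 1 | 3.65 | 89.7% | 26 |
| 0.9 | 0.95 | 3.56 | 91.1% | 24 |
| 0.7 | 0.85 | 3.37 | 93.8% | 22 |
| 0.5 | 0.75 | 3.16 | 96.1% | 19 |

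The gain is about 1 to 6 points.

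**3. The two allocation factors.** Dynamic allocation was simulated as minimisation on sex and vessel number: biased coin 0.8, 52 evaluable patients, assumed prevalences of 30% for one sex and 40/30/30% for the vessel classes, 10,000 null runs and 4,000 runs at 3.33 per setting.

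| R² of the factors | type I error, unadjusted | type I error, factors in model | power, unadjusted | power, factors in model |
|---|---|---|---|---|
| 0 | 4.9% | 4.8% | 89.3% | 89.5% |
| 0.05 | 4.1% | 4.6% | 89.5% | 90.0% |
| 0.10 | 4.1% | 5.2% | 90.3% | 92.1% |
| 0.20 | 3.2% | 5.0% | 91.8% | 94.7% |
| 0.30 | 2.5% | 5.2% | 92.8% | 96.9% |

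A repeat simulation gave 2.0% for the unadjusted test at R² = 0.30, so 2 to 2.5% is a fair statement of that end. The power difference in the table runs from 0 to about 4 points (96.9 − 92.8 = 4.1); allowing for simulation error, about 0 to 5.

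**4. Separating the two sources.** With the factors set to R² = 0 and a baseline covariate explaining 15% of the change, leaving baseline out gave a type I error of 5.2%, which is nominal within simulation error. Conservatism therefore comes only from the factors that the allocation balances.

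**5. Cost of adjusting for nothing.** With no predictive covariate at all, power was 89.3% unadjusted and 88.6% with all of them in the model, a cost of less than one point.

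**The case against.** The strongest reply is that section 3.3 is a condensed description. It does not call the analysis of variance one-way or exclude sex and vessel number, and covariates are often fixed in an analysis plan, which is not shown here. This stands in part: if such a plan already specifies the adjusted model, the sponsor need only say so. But the article does not leave the test open. It names a test family, offers a nonparametric alternative that would not ordinarily carry covariates, and sizes the trial for an unadjusted comparison. Replacing that with a better method is a substantive change.

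Four stronger readings are tempting, and the article does not support them.

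- A reader might infer that baseline is ignored. It is not: the endpoint is a change from baseline, so baseline enters through the outcome. It is only not used as a covariate.
- A reader might infer that the test is conservative as a matter of fact. That needs sex and vessel number to predict the change in peak VO2. Section 2.5.1 justifies them by recurrence of cardiovascular events and prognosis after intervention, not by exercise capacity.
- A reader might infer that the planned power is missed. It is essentially met without adjustment (step 1).
- A reader might infer that balancing is useless unless the factors are modelled. In the table, unadjusted power rises from 89.3% to 92.8% as R² grows, so balance alone yields part of the gain.

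A further limit stands: the formula (1 + r)/2 applies to absolute change. If the rate of change means a percentage, the baseline figures do not carry over directly.

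**Conclusion.** This is a point of efficiency and of matching the analysis to the design, not of validity. The stated comparison does not inflate false positives. Relative to an adjusted model it forgoes about 1 to 6 points of power at 3.33 through baseline (r from 0.9 to 0.5, absolute change, equal variances). It forgoes about 0 to 5 points through the allocation factors, with a true type I error between about 5% and 2 to 2.5% (R² from 0 to 0.30, minimisation as simulated). If the factors do not predict the change in peak VO2, nothing is lost through them. Neither r nor R² is given in the article, so the direction is firm but the size is conditional. The change is worth making because the trial is small and adjustment costs almost nothing, even when the covariates turn out to be weak.

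**What to change.** Before unblinding, specify one primary analysis: an ANCOVA of week-12 peak VO2 (or its absolute change; with baseline in the model the treatment estimate is the same) on treatment, with baseline peak VO2, sex and number of diseased vessels (single, double, multiple) as covariates. Report the adjusted mean difference with its 95% confidence interval. Keep a rank-based analysis as a sensitivity analysis, in place of the open choice between analysis of variance and a nonparametric test. State whether rate of change means absolute or percentage change, so that the model and the sample-size scale agree.

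The cost is wording. Baseline peak VO2 is needed for the endpoint and the two factors for allocation, so no new data are required. The model spends four further degrees of freedom (one for baseline, one for sex, two for vessel number), leaving 46 of 50 with 52 evaluable patients. The sample size need not change.
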